## NIS Labs Protocol 181-002. Rapid immune modulating effects: Clinical proof-of-concept study.

### 1 Purpose

The goal for this clinical proof-of-concept study is to compare acute immune effects of a novel nutraceutical blend to a placebo.

### 2 Study

#### 2.1 Clinical Study Design

For this clinical study, human subjects will be tested following an **established placebo-controlled, randomized, double-blinded, cross-over study design**. Specifically, the study design has been used in previous clinical studies on immune modulating products including the yeast-based fermentate Epicor, a bovine colostrum-based peptide- and oligosaccharide-rich extract Immunel, the algae-based extract for stem cell support StemEnhance, and an aloe-based folk medicine formulation from Madagascar. Recently, the NIS Labs' team also published on changes to lymphocyte trafficking, specifically stem cell subsets, using this study design when consuming placebo versus a polyphenol-rich extract from Sea Buckthorn from Tibet.

Below is a simplified diagram illustrating the involvement of each human subject, where each study participant will be tested on two different clinic days.

[figure not shown]

**ARGUS IRB, INC.**

Figure 1. Diagram showing the involvement of each human subject. Study participants will be tested on two different clinic days. The sequence of test products shown here is an example only since the sequence will be randomized.

The test parameters we will evaluate do not necessarily stay constant, even over a few hours, since they are related to people's metabolism, individual circadian rhythms, and other normal physiological parameters. Therefore, studies of this nature must include a placebo test day, allowing *within-subject* analysis of changes between the test days for each person. This very much strengthens the data analysis from this type of study. In the absence of a placebo test day, we consider the data inconclusive since changes cannot be interpreted as being related to product intake.

In light of previous data on products such as EpicorI and Immunel,II some differences were seen at 1 versus 2 hours, and it is ideal to perform testing at both time points. In addition, data will also be collected after 3 hours.

## 2.2 Outcome Measures

**Primary outcome measure:** Immune surveillance: Trafficking and activation of immune cells in vivo.

## 3 Study Population

### 3.1 Subjects

24 healthy subjects of either gender will be enrolled after IRB-approved, written informed consent. The inclusion/exclusion profile for a study of this nature is not trivial, and each potential study participant is carefully evaluated prior to enrollment. To minimize anticipatory stress and apprehension during initial clinic visits for the study, each study participant must either have participated in previous studies at our facility or must attend a visit where we go through the study procedures, prior to a clinical study day.

### 3.2 Inclusion Criteria

- Healthy adults;
- Age 18-75 years (inclusive);
- BMI between 18.0 and 34.9 (inclusive);
- Veins easy to see in one or both arms (to allow for the multiple blood draws);
- Willing to comply with study procedures, including:
  - Maintaining a consistent diet and lifestyle routine throughout the study;
  - Consistent habit of bland breakfasts on days of clinic visits;
  - Abstaining from exercise and nutritional supplements on morning of study visit;

**APPROVED**

**AUG 13 2021**

**ARGUS IRB, INC.**

- Abstaining from use of coffee, tea, and soft drinks for at least one hour prior to a clinic visit;
- Abstaining from music, candy, gum, computer/cell phone use, during clinic visits.

### 3.3 Exclusion Criteria

- Previous major gastrointestinal surgery (absorption of test product may be altered) (minor surgery not a problem, including previous removal of appendix and gall bladder);
- Taking anti-inflammatory medications on a daily basis;
- Currently experiencing intense stressful events/ life changes;
- Currently in intensive athletic training (such as marathon runners);
- Cancer during past 12 months;
- Chemotherapy during past 12 months;
- Currently treated with immune suppressant medication;
- Diagnosed with autoimmune disorders e.g. systemic lupus erythematosus, hemolytic anemia;
- Donation of blood during the study or within the 4 weeks prior to study start;
- Have received a cortisone shot within past 12 weeks;
- Immunization during last month;
- Currently taking antipsychotic, hypnotic, or anti-depressant prescription medication;
- Ongoing acute infections (including teeth, sinus, ear, etc);
- Participation in another clinical trial study during this trial, involving an investigational product or lifestyle change;
- An unusual sleep routine (examples: working graveyard shift, irregular routine with frequent late nights, studying, partying);
- Unwilling to maintain a constant intake of supplements over the duration of the study;
- Anxiety about having blood drawn;
- Women of childbearing potential: Pregnant, nursing, or trying to become pregnant;
- Known food allergies related to ingredients in active test product or placebo.

**APPROVED**

**AUG 13 2021**

**ARGUS IRB, INC.**

Prescription medication will be evaluated on a case-by-case basis.

### 3.4 Consumable Test Products

The active test product and the placebo will be provided by study sponsor. The active test product contains mushrooms, rosemary, and aloe, so we will ask potential study participants about food sensitivities to those ingredients.

On each clinic day, immediately after the baseline blood draw, participants will be given a single dose of either the active test product or a placebo, in the presence of the clinic staff. Participants will consume the capsules with water and a few bland soda crackers to stimulate digestive function.

### 3.1 Study environment

The study of acute changes to levels, activation status, and functionality of immune cells is not trivial. All test parameters undergo circadian changes, and are negatively affected by stress, adrenaline, certain medications, lack of sleep, and recent illness. The study participants will be instructed to call and reschedule a certain clinic day if they feel that any of these things are reasons to do so.

Also, the study environment is kept controlled for stressors. Cell phones are turned off at entry to clinic. Clinic phones and door chimes are off. Sensory input such as music, coffee/food smells, noises, etc., will be eliminated or kept to an absolute minimum. In order to keep volunteers in a state of mind we refer to as 'perpetually bored', but not falling asleep, they are offered a choice of light reading, crossword puzzles, or cards to play solitaire.

Upon arrival on the morning of each clinic day, participants will rest quietly for 1 hour prior to baseline blood draw. This resting period is crucial to gain representative baseline data. During this time, questionnaires will be completed to monitor previous meals, snacks, exercise, stressors, and recent sickness. Then a product will be fed to the participants. Three more blood samples will be drawn at 1, 2, and 3 hours after consumption.

**APPROVED**

**AUG 13 2021**

### 3.2 Study Procedures

**ARGUS IRB, INC.**

#### 3.2.1 Explanation of clinical study procedures

In a clinical trial to monitor immune activating events, we expect a cascade of events, starting by activation of immune cells in the gut, systemic changes to cytokine levels, changes to immune cell trafficking (enhanced immune surveillance), followed by immune surveillance in

tissue throughout the body, and possibly re-entry of activated immune cells back into the blood circulation.

Blood samples offer a convenient window into the immune events happening after a product is consumed. We do not have convenient windows into what may happen at the initial gut activation, but we envision this is similar to events in vitro. We do not have windows into tissue and thus cannot monitor downstream events after immune cells migrate from blood into tissue to scavenge for microbial invaders and perform innate and adaptive types of immune responses. Therefore, we mimic this by taking some of the blood samples and challenging the immune cells ex vivo (outside the body) with microbial mimetics.

The testing described in **Section 3.3.1** aims to monitor rapid changes in the types and activation status of immune cells seen in the blood circulation. Increases versus decreases in numbers of immune cells in the blood is a measure of cellular trafficking in and out of the blood stream. We are looking for subtle events, where any systematic changes observed in a majority of the study participants after consuming the test product suggests immune activating events are induced.

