**APPROVED**

**AUG 18 2021**

**ARGUS IRB, INC.**

### 3.3.1 NK/T cell panel

Cells are stained with the T cell marker CD3 and the CD56 and CD57 markers, as well as the two activation markers CD69 and the interleukin-2 receptor CD25. This allows analysis of numbers of the following types of immune cells in the blood circulation at each time point in the study:

- CD3-negative, CD56-positive **NK cells**;
- CD3+ CD56+ **NKT cells**;
- CD3+ CD56- **T lymphocytes**;
- CD3-CD56- **non-NK, non-T lymphocytes**;
- CD3-CD57+ **NK cells**
- CD3- CD56+CD57+ **NK cells**
- **Monocytes** (identified by forward/side scatter profile);

During analysis, expression levels will be determined for the activation molecule **CD69** and growth factor receptor **CD25** on the surface of the cell populations listed above.

**Note:** Immune surveillance involves the constant recirculation of lymphocyte subsets, including NK and T cells. The trafficking shows a distinct circadian rhythm and is affected by a person's metabolic state. When comparing the acute effects of a consumable immune modulating product on immune surveillance, it is important to have a placebo control test day, to account for a given person's normal circadian changes at the time of the day of testing.

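### The protocol's one interpretive criterion, a systematic change in a majority after the test product, names no placebo contrast, direction or error-controlled threshold, and conflicts with its own within-subject design logic

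*Protocol*

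**What the plan says.** Section 3.2.1 (Explanation of clinical study procedures) says that the study looks for subtle events and that "any systematic changes observed in a majority of the study participants after consuming the test product suggests immune activating events are induced". The sentence just before it covers cell counts in both directions: "Increases versus decreases in numbers of immune cells in the blood is a measure of cellular trafficking in and out of the blood stream".

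Other sections set out how changes can be attributed to the product:

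- Section 1 gives the goal as a comparison of acute immune effects with placebo.
- Section 2.1 (Clinical Study Design): "studies of this nature must include a placebo test day, allowing *within-subject* analysis of changes between the test days for each person", and "In the absence of a placebo test day, we consider the data inconclusive since changes cannot be interpreted as being related to product intake".
- Section 3.3.1 (NK/T cell panel), in its note: "it is important to have a placebo control test day, to account for a given person's normal circadian changes at the time of the day".
- Section 3.1 (Study environment): "All test parameters undergo circadian changes, and are negatively affected by stress, adrenaline, certain medications, lack of sleep, and recent illness".

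Section 3.1 (Subjects) sets the size: "24 healthy subjects of either gender will be enrolled after IRB-approved, written informed consent". Each clinic day has three post-dose samples: "Three more blood samples will be drawn at 1, 2, and 3 hours after consumption". The primary outcome in Section 2.2 is the trafficking and activation of immune cells in vivo, with no single variable or time point named.

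**The concern.** The Section 3.2.1 sentence links an observed result to the conclusion that the product induced immune activation. As worded, it lacks three things that such a link needs.

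1. **A placebo contrast.** It refers to change after the test product only. Section 2.1 holds that such change, without a placebo day, cannot be put down to the product.
2. **A direction.** Any systematic change counts. Rises and falls in cell numbers are both trafficking by the preceding sentence, yet the conclusion drawn is activation.
3. **A threshold with a known error rate.** A majority is a low bar with 24 people, and *systematic* is not defined.

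Ordinary movement over a clinic morning could therefore be reported as immune activation with the protocol cited in support. A sound test in a separate analysis plan would not remove the problem, because this sentence would then conflict with that test.

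**Working it through.** The protocol gives no error rate for this criterion, so there is no stated figure to reproduce.

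**Inputs from the protocol.** 24 participants (Section 3.1, Subjects); a majority (Section 3.2.1), which for 24 is at least 13; three post-dose time points (Section 3.1, Study environment).

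**Assumptions not in the protocol.** Complete data on 24 independent participants, no ties, and each participant equally likely to rise or fall when the product does nothing.

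**Step 1: one variable, one time point.** Let X be the number who rise, X ~ Binomial(24, 0.5).

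- Named direction: P(X ≥ 13) = 0.4194.
- Either direction: 2 × 0.4194 = 0.8388. Check: only an exact 12–12 split fails, so 1 − C(24,12)/2^24 = 1 − 2,704,156/16,777,216 = 1 − 0.1612 = 0.8388.

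**Step 2: one variable, three time points.**

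- A majority in either direction at one or more time points: 1 − (1 − 0.8388)^3 = 0.996 if independent; about 0.995 by simulation when the three changes share one baseline value.
- A stricter reading of *systematic*, the same-direction majority at all three time points: about 0.29 by simulation with a shared baseline (correlation 0.5 between changes). If the three changes were independent it would be 2 × 0.4194^3 = 0.15. If they moved in complete lockstep it would return to 0.84.

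**Step 3: does the placebo contrast alone cure it?** No. With no product effect, the active-minus-placebo difference is also equally likely to be positive or negative, so 13 of 24 again gives 0.42 and 0.84. These figures come from the majority bar.

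**Step 4: what omitting the contrast adds.** Suppose normal drift moves a share p of people the same way with no product effect. The protocol gives no value for p, so 0.6 to 0.8 is an assumed range.

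| p | P(majority in the drift direction) | P(majority in either direction) |
|---|---|---|
| 0.5 (no drift) | 0.419 | 0.839 |
| 0.6 | 0.787 | 0.901 |
| 0.7 | 0.969 | 0.980 |
| 0.8 | 0.999 | 0.999 |

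**Step 5: what count would carry evidence.** Exact two-sided sign test on 24 differences, p = 2 × P(X ≥ k):

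| k of 24 | two-sided p |
|---|---|
| 13 | 0.839 |
| 16 | 0.152 |
| 17 | 0.064 |
| 18 | 0.023 |

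Eighteen is the smallest count below 5%.

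**Step 6: number of comparisons.** Section 3.3.1 alone lists 7 populations, each with a count, CD69 and CD25, at 3 post-dose times: 7 × 3 × 3 = 63, before the other two panels. An unadjusted 5% test at three independent time points of one variable already gives 1 − 0.95^3 = 0.14.

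**The case against.** The strongest reply is that this is explanatory prose and not a decision rule. It closes a narrative section, its verb is *suggests*, and it gives no variable, cut-off or significance level. Formal criteria may sit in an analysis plan that is not shown. Sections 1, 2.1 and 3.3.1 plainly require the placebo comparison, every participant has a placebo day, and the sentence never says that day is to be set aside. On this view it is silent and should be read together with the design.

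Much of that stands. A reader might infer that the protocol ignores the placebo day, but that is true of this sentence only. A reader might also take the sentence as the trial's formal rule for claiming efficacy, and the text does not go that far. The 84% must not be presented as the cost of leaving out placebo, since Step 3 shows that it comes from the bare either-direction majority. It also depends on reading *systematic* loosely; stricter readings give 0.42 or about 0.29. The drift figures apply only if the placebo day goes unused, and their range is assumed. Finally, a reader might infer that a fall in CD69 or CD25 would be called activation. The sentence on increases and decreases concerns cell numbers, so that is inference.

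The reply does not dispose of the wording itself. Sections 1, 2.1 and 3.3.1 say how to compare and when attribution is possible, but none says what observed result would suggest an effect. Only Section 3.2.1 does, and it omits the contrast the others call essential. The concern is with what the sentence states, so an unseen analysis plan does not answer it.

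**Conclusion.** The point holds as a defect in one interpretive sentence that is out of step with the rest of the protocol. It does not show that the trial lacks a placebo-controlled analysis.

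The criterion has no placebo contrast, no direction and no error-controlled threshold. For an inert product it would be met far more often than 5% on every reading examined: 0.84 in either direction and 0.42 in a named direction, per variable and time point, and about 0.29 even when all three time points must agree. The first two figures are exact given 24 complete, independent participants, no ties and symmetric change. The third is simulated under a shared baseline and would be 0.15 under independence. Two separate weaknesses are at work. The majority bar is too low even for active-minus-placebo differences, and leaving out the placebo contrast adds exposure to the circadian drift that the protocol itself describes.

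**What to change.** Replace the Section 3.2.1 sentence with wording such as: *An effect of the product is inferred only from the within-participant difference (change from baseline on active minus change from baseline on placebo), tested two-sided at 5% for one named variable at one named time point. All other variables and time points are exploratory, or are tested with adjustment for multiplicity.* The sponsor should name the variable and time point before unblinding.

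In addition:

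- State the direction of every reported change, and describe changes in cell counts as trafficking rather than as activation in themselves.
- Do not limit *activation* to CD69 and CD25. Section 3.3.2 (T/B cell panel) also treats co-expression of the CD45 isoforms as a sign of recent activation.
- If participant counts are shown, count those whose active change exceeds their own placebo change, and give the exact sign-test p-value (18 of 24 gives 0.023; 17 of 24 gives 0.064). Do not offer a simple majority as evidence.

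The cost is protocol wording, with no new data or visits. The downside is that fewer changes can be called effects. The sign count should remain a descriptive supplement to the test of the differences: if 70% of participants truly exceeded their placebo change (an assumption), 18 of 24 would be reached only 39% of the time.

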**APPROVED**

**AUG 13 2021**

**ARGUS IRB, INC.**

### 3.2.2 Table Over Study Procedures

|                                     | Screen | Week 1       |           |        |        | Week 2 |              |           |        |        |        |
|-------------------------------------|--------|--------------|-----------|--------|--------|--------|--------------|-----------|--------|--------|--------|
|                                     |        | Upon arrival | Base line | 1 hour | 2 hour | 3 hour | Upon arrival | Base line | 1 hour | 2 hour | 3 hour |
|                                     |        |              |           |        |        |        |              |           |        |        |        |
| Screening and enrollment            |        |              |           |        |        |        |              |           |        |        |        |
| Height (question)                   | X      |              |           |        |        |        |              |           |        |        |        |
| Weight (question)                   | X      |              |           |        |        |        |              |           |        |        |        |
| Medical/surgical history            | X      |              |           |        |        |        |              |           |        |        |        |
| Health status interview             | X      |              |           |        |        |        |              |           |        |        |        |
| Current medications                 | X      |              |           |        |        |        |              |           |        |        |        |
| Current supplements                 | X      |              |           |        |        |        |              |           |        |        |        |
| Recent illness                      | X      |              |           |        |        |        |              |           |        |        |        |
| Clinic days                         |        |              |           |        |        |        |              |           |        |        |        |
| Pregnancy test (females)            | X      |              |           |        |        |        |              |           |        |        |        |
| Height                              | X      |              |           |        |        |        | X            |           |        |        |        |
| Weight (check BMI is in range)      | X      |              |           |        |        |        | X            |           |        |        |        |
| Informed consent                    | X      |              |           |        |        |        |              |           |        |        |        |
| Daily Intake Questionnaire          | X      |              |           |        |        |        | X            |           |        |        |        |
| 5-Question Questionnaire            |        | X            | X         | X      | X      |        |              | X         | X      | X      | X      |
| Blood pressure                      |        | X            | X         | X      | X      |        |              | X         | X      | X      | X      |
| Blood draw (1 pink tube)            |        | X            | X         | X      | X      |        |              | X         | X      | X      | X      |
| Feed test product                   |        | X            |           |        |        |        |              | X         |        |        |        |
| Lab tests on clinic days            |        |              |           |        |        |        |              |           |        |        |        |
| Immune cell numbers and activation* |        | X            | X         | X      | X      |        |              | X         | X      | X      | X      |
| Plasma banking**                    |        | X            | X         | X      | X      |        |              | X         | X      | X      | X      |
| OTHER                               |        |              |           |        |        |        |              |           |        |        |        |
| Adverse events***                   |        |              |           |        |        | X      |              |           |        |        | X      |

\*The immune phenotyping evaluates immune surveillance and cellular activation in vivo.

Panels for NK cell activation, B and T cell activation, and numbers of gamma delta T cells are evaluated.

\*\*Plasma banking allows subsequent tests to be added later without repeating the clinical study.

\*\*\*Clinic staff takes note of anything observed that may be relevant to understanding the data.

For example information a participant offers that was not prompted by the daily intake questions, or any other signs of stress, depression, or agitation.

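### Adverse events are recorded as end-of-visit staff notes judged by relevance to the data, with no requirement to record other harms and no systematic capture of reactions after the participant leaves

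*Protocol*

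**What the plan says.** The procedures table in Protocol section 3.2.2 has a row labelled "Adverse events". As the table reads, it carries two marks, one under the 3-hour column of Week 1 and one under the 3-hour column of Week 2. The row's footnote says: "Clinic staff takes note of anything observed that may be relevant to understanding the data". It continues: "For example information a participant offers that was not prompted by the daily intake questions, or any other signs of stress, depression, or agitation".

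Other passages set the exposure and the contact time:

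- Section 3.4: on each clinic day "participants will be given a single dose of either the active test product or a placebo, in the presence of the clinic staff".
- Section 3.1 (Study environment): "Three more blood samples will be drawn at 1, 2, and 3 hours after consumption".
- Caption of Figure 1 (section 2.1): "Study participants will be tested on two different clinic days".

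Health information is also collected outside the adverse-event row. During the rest period after arrival on each clinic day, section 3.1 (Study environment) provides: "During this time, questionnaires will be completed to monitor previous meals, snacks, exercise, stressors, and recent sickness". The table also schedules blood pressure and a 5-question questionnaire alongside every blood draw. The protocol does not give the content of that questionnaire.

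The table of contents lists no section on safety or adverse events.

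**The concern.** A row with this label would normally be where harms to participants are recorded. Here the footnote gives staff a different test, namely whether an observation helps to explain the laboratory results. That is a useful note on assay quality, but it is not a rule for collecting adverse events. A staff member following it could properly leave out a rash or an upset stomach judged to have no bearing on flow cytometry.

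Timing is the second weakness. The entry falls at the last scheduled contact of each day, and no rule covers what happens later. The product is described in section 1 as a novel blend, and section 3.4 plans to ask candidates about sensitivity to three of its ingredients. Screening of that kind can find only sensitivities that people already know about.

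At stake is the tolerability information the trial could yield. A placebo-controlled crossover lets each participant's experience on active product be compared with the same person's experience on placebo, provided events are asked for in the same way in both periods and tied to the product taken. Without that, a report of few or no events could not be separated from the way they were collected.

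**Working it through.** The protocol states no figure on this point, so there is none to reproduce. The check sets the passages side by side and counts what is scheduled.

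**1. How often the row is completed.** There are 2 marks per participant (Week 1 at 3 hours, Week 2 at 3 hours). With 24 participants (section 3.1, Subjects) that is 24 × 2 = 48 entries in the whole trial. In the extracted table the Week 1 marks of several other rows (blood draw, blood pressure, feeding) sit one column to the left of their Week 2 positions, probably from the PDF reading. The adverse-event row is not shifted.

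**2. What must be recorded.**

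| Kind of event | Required by the footnote? |
|---|---|
| Sign of stress or agitation seen by staff | Yes, a listed example |
| Volunteered remark that may help explain the data | Yes, a listed example ("For example information a participant offers that was not prompted by the daily intake questions") |
| Physical reaction judged relevant to the data | Yes, by the general wording |
| Physical reaction judged not relevant to the data | Not required, though not forbidden |

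**3. What is captured after the participant leaves.**

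| Period | Route by which a later reaction could surface | Linked to the adverse-event row? |
|---|---|---|
| After the Week 1 visit | Recent-sickness question on arrival in Week 2 | No rule links them |
| After the Week 2 visit | None scheduled | Not applicable |

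Section 3.1 (Study environment) also lets participants call to reschedule a clinic day, with recent illness among the reasons. Nothing there says that such a call is logged as an event.

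**4. Size of the gap in time.** The protocol says only Week 1 and Week 2. Assume 7 days between clinic days, which is 7 × 24 = 168 hours. Planned observation after the first dose is then 3 / 168 = 1.8% of the interval. At 5 days it is 3 / 120 = 2.5%, and at 9 days 3 / 216 = 1.4%. After the second dose, planned observation ends at 3 hours whatever the interval.

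**5. Which doses are affected most.** All 24 second doses lack any later contact. The sequence is randomized, but the ratio is not given. If the two sequences are balanced, 12 of those 24 doses are active product and 12 are placebo. Under simple randomization with equal probability, the standard deviation of the active count is √(24 × 0.5 × 0.5) = 2.45, so 12 ± 1.96 × 2.45 gives roughly 7 to 17. Either way, both products are followed less closely in Week 2 than in Week 1. The main effect is loss of information, not an evident bias towards one product.

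**The case against.** Three stronger readings are tempting, and the documents support none of them.

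- *A reader might infer that nobody asks what happened after the first visit.* The arrival questionnaires on each clinic day cover recent sickness, so a reaction after Week 1 may well be mentioned in Week 2. What stands is that the answer is gathered to interpret the data and is not carried into the adverse-event record.
- *A reader might infer that participants are watched at one moment only, and never prompted.* The 3-hour mark may be an end-of-visit entry covering the whole supervised visit. Blood pressure and a questionnaire accompany every draw. Because that questionnaire's content is not given, it cannot be said either to ask about symptoms or not to.
- *A reader might infer that harms unrelated to the assays are certain to be lost.* The footnote speaks of anything observed, and its examples are introduced as examples. A visible reaction on the day could be noted under it. The supportable statement is that noting it is not required.

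There are further arguments in the plan's favor. Known allergies to ingredients of either product are an exclusion criterion (section 3.3), each participant takes a single dose of active product, and the stated purpose and primary outcome concern immune effects, not safety. Consent pages are not available, so instructions to participants about reporting later reactions cannot be assumed absent. These points limit the seriousness. They do not remove the fault, because the protocol chose to have an adverse-event row and gave it a criterion suited to something else. An unseen statistical analysis plan does not cure this either: it can say how events are tabulated, but it cannot recover events that staff were not told to collect.

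**Conclusion.** The point holds in this form. Adverse events are captured through staff notes entered at the 3-hour point of each clinic day and judged by relevance to the data. Harms that do not bear on the assays need not be recorded. Later reactions are not systematically captured: after Week 1 only an unlinked recent-sickness question could bring them out, and after Week 2 nothing is scheduled.

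The gap is one of coverage: 2 entries per participant, and no planned contact beyond 3 hours after any of the 24 second doses. How many events would go unrecorded cannot be estimated, because the protocol gives no event rate. The conclusion rests on the column positions of the adverse-event row as extracted, on the table of contents showing that no safety section exists elsewhere, and on no reporting instruction in the removed consent pages filling the gap.

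The primary outcome is not affected. This is a real defect of moderate weight that is cheap to correct before the first participant is dosed.

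**What to change.** 1. Define an adverse event in the protocol as any untoward event after the first dose, whether or not it bears on the data or is thought related to the product.
2. Ask one standard open question at each existing post-dose draw and on arrival in Week 2, worded the same on both clinic days.
3. Record the answers as adverse events, including any recent sickness reported at Week 2 arrival.
4. Tabulate events by the product taken.
5. Keep the staff observation note, but as a separate row under its own name.
6. Optionally, add one brief phone or e-mail contact after the Week 2 visit. This is the only item that closes the gap after the second dose.

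Cost: the question is asked 3 times on each of 2 clinic days plus once at Week 2 arrival, so 3 × 2 + 1 = 7 times per participant, all at contacts that already exist. The optional follow-up is 24 short contacts. The downside is a little staff time. No dose, assay or visit changes.
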